### Study Design

The EZI-PrEP study will be a 2×2 factorial, 4-arm, open-label, multi-center, randomized, controlled, noninferiority trial. Study participants will be randomized to 1 of 4 arms: (1) in-clinic monitoring every 3 months (standard of care), (2) in-clinic monitoring every 6 months, (3) online monitoring every 3 months, or (4) online monitoring every 6 months (Figure 1). The study will be implemented at SHCs in Amsterdam, Rotterdam-Rijnmond, Haaglanden, and Gelderland-Zuid (Figure 2). For each individual participant, the planned observation time is 24 months, starting after eligibility screening and enrollment.

All study participants will receive access to a smartphone app (the “EZI-PrEP app”), which contains a diary. Participants will be required to complete this diary daily during the first 18 months of the study period. This information will be used to measure the primary outcome (ie, unprotected acts). DBSs will be collected at months 6 and 12. Routine clinical data registered during PrEP monitoring visits and any additional STI testing or treatment visits from inclusion until the final monitoring visit at month 24 will be retrieved from the national STI surveillance system. Participants will be requested to complete 5 questionnaires (at baseline and at 6, 12, 18, and 24 months) to collect data on PrEP intake; sexual behavior; psychosocial characteristics; and the experiences, acceptability, and usability of the interventions. We will extract automatically registered data on app usage from the app.

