### Randomization

Participants will be randomized (stratified by PHS and by PrEP experience, that is, those starting or restarting PrEP, and current PrEP users) to 1 of 4 study arms in permuted blocks of 4. Randomization will be performed by a statistician of PHS Amsterdam who is not part of the EZI-PrEP study team at initiation of the study, using Stata Intercooled 15.1 (StataCorp). Sequentially numbered and colored nontransparent envelopes will be made, containing a code for the study arm. Each PHS will receive 2 sets of envelopes, red ones for those starting or restarting PrEP and blue ones for current PrEP users. During the enrollment interview, in the presence of the participant and dependent on their PrEP experience, the health care provider will open the next envelope to reveal the study arm and study number.

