#### Study Questionnaires

The first 4 questionnaires (ie, at baseline, and 6, 12, and 18 months) will ask about PrEP intake, sexual behavior, risk perception related to STIs and HIV infection, and STI testing at facilities other than SHCs. We will include several psychosocial measurements in the questionnaires (summarized in Table 2). The questionnaire at month 12 will include questions on social norms with respect to PrEP use, loneliness, and the presence of social support systems. To investigate the usability and acceptability of the PrEP care modality, we will include questions based on Davis’ model of technology acceptance [52] at months 6, 12, and 18. These questionnaires will also include questions regarding experiences with PrEP care and to what extent participants felt supported in their PrEP use. To assess the usability and acceptability of online-mediated PrEP care specifically, we will include the system usability scale [53] at month 18 for online study participants. We will also ask them to rate the different steps during their online PrEP care. The fifth (and last) questionnaire, at month 24, will focus on the quality of PrEP care within the EZI-PrEP study and in the Netherlands in general, as well as the time and cost investments of study participants in receiving PrEP care.

**Table 2 table2:** Overview of psychosocial measurements within the EZI-PrEP study in each survey round.

Scale	Abbreviation	Aspect measured	Baseline survey (month 0)	Follow-up survey			
				Month 6	Month 12	Month 18	Month 24
Self-reported habit index	SHI	Habit formation	✓	✓	✓	✓	
Patient Health Questionnaire-9	PHQ-9	Severity of depressive symptoms	✓	✓	✓	✓	
Generalized Anxiety Disorder Assessment	GAD-7	Generalized anxiety disorder	✓	✓	✓	✓	
Sexual compulsivity scale	SCS	Sexual compulsivity	✓		✓		
Alcohol Use Disorders Identification Test	AUDIT	Problematic alcohol use	✓			✓	
Drug Use Disorders Identification Test	DUDIT	Problematic drug use	✓			✓	
Perceived stress questionnaire	PSQ20	Perceived stress		✓	✓	✓	
Brief Resilience Scale	BRS	Resilience		✓			
Cognitive Emotion Regulation Questionnaire	CERQ-short	Coping skills			✓		
HEXACO^a^ Personality Inventory-Revised	HEXACO-PI-R	Conscientiousness			✓		

^a^HEXACO is an acronym for “Honesty-humility,” “Emotionality,” “Extraversion,” “Agreeableness,” “Conscientiousness,” and “Openness to experience.”

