#### Secondary Outcomes

We will assess intracellular concentrations of TFV-DP and FTC-TP using DBSs collected at month 12 in all participants using daily PrEP. The lower limit of detection is determined as 25 fmol/punch and 50 fmol/punch for TFV-DP and FTC-TP, respectively. The distribution of the intracellular concentrations of TFV-DP and FTC-TP will be compared between daily PrEP users in (1) online PrEP care versus in-clinic PrEP care and (2) monitoring every 6 months versus monitoring every 3 months, using a rank-sum test. In a secondary analysis, the log-transformed values will be compared using a linear regression.

The incidence rates of HIV infection and TFV/FTC-resistant HIV infection, and the incidence rates of bacterial STIs (ie, chlamydia, gonorrhea, and syphilis), HCV infection, and eGFR of less than 60 mL/min/1.73m^2^ will be assessed. The incidence rates are calculated by dividing the number of diagnoses by the person-years of observation. The incidence rates will be compared for (1) online PrEP care versus in-clinic PrEP care and (2) monitoring every 6 months versus monitoring every 3 months.

Retention in PrEP care is defined as having had a PrEP prescription no longer than 8 months ago. Participants will be considered lost to follow-up when they do not complete a PrEP monitoring visit at month 18 within 2 months of the planned date. They will be regarded as lost to follow-up from the date of the last contact with the study (ie, completed a diary, questionnaire, or consultation). We will compare proportions of participants who are retained in PrEP care or are lost to follow-up for (1) online PrEP care versus in-clinic PrEP care and (2) monitoring every 6 months versus monitoring every 3 months, using the Pearson χ^2^ test.

Satisfaction with PrEP care will be compared between study arms. Furthermore, we will analyze how usability of the online PrEP service differs between online-mediated PrEP care every 3 months and every 6 months. For these analyses, we will use the Wilcoxon signed-rank test of the Likert score outcomes.

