### Power and Sample Size Calculation

We assume that the primary outcome measure of unprotected acts will be Poisson distributed with the total number per 100 person-years given as an incident rate (λ) and the total time during monitoring (*t*). We define the incidence rate in the experimental arm as λ_e_ and the incidence rate in the control arm as λ_c_. We aim to reject the null hypothesis that the ratio λ_e_/λ_c_ is greater than or equal to a predetermined noninferiority ratio (r). We consider that a noninferiority ratio of 1.8 is able to preserve clinically acceptable noninferiority bounds with increasing λ.

In a previous PrEP study in the Netherlands (Amsterdam PrEP demonstration project [“AMPrEP study”]), the overall incidence rate of unprotected acts was 78/100 person-years [50]. The AMPrEP study included participants with a high number of sex partners and very high incidence of bacterial STIs. Participants of the NPP have reported fewer casual sex partners and have a lower incidence of bacterial STIs [55]. The EZI-PrEP participants are therefore expected to have fewer unprotected sex acts than the AMPrEP participants. We expect the incidence rate of unprotected acts in the experimental arm (λ_e_) and control arm (λ_c_) to be at least 36/100 person-years. We also assume a median monitoring time of 18 months. Using a Bonferroni-corrected 1-sided type 1 error of 0.0125 (=0.025/2 for a total of 2 comparisons), we will need 368 participants to have 90% power to demonstrate noninferiority using the test statistic based on maximum likelihood estimators from Stucke and Kieser [56]. If λ is higher than 36/100 person-years, we will have sufficient power to demonstrate noninferiority. Considering expected loss to follow-up, we have increased the target sample size by 20%, and thus, the total required sample size is 442.

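### Satisfaction and usability are to be compared between independent randomised arms with the Wilcoxon signed-rank test, which needs paired data

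*Protocol article*

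**What the plan says.** The last paragraph of Secondary Outcomes sets out two comparisons. The first is "Satisfaction with PrEP care will be compared between study arms". The second is that "we will analyze how usability of the online PrEP service differs between online-mediated PrEP care every 3 months and every 6 months", which means arm 3 against arm 4. One method is then fixed for both: "For these analyses, we will use the Wilcoxon signed-rank test of the Likert score outcomes".

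Study Design describes parallel allocation: "Study participants will be randomized to 1 of 4 arms". Randomization adds that participants are allocated "to 1 of 4 study arms in permuted blocks of 4", stratified by public health service region (PHS) and PrEP experience. Study Questionnaires places the main usability instrument at a single time point: "we will include the system usability scale [53] at month 18 for online study participants".

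Earlier in Secondary Outcomes, drug concentrations in dried blood spots are compared for online v in-clinic care and for "monitoring every 6 months versus monitoring every 3 months, using a rank-sum test".

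**The concern.** The signed-rank test takes one difference per unit, either two measurements on the same person or two members of a matched pair, and asks whether those differences centre on zero. The stated comparisons are between different people in different arms, so there is no difference to rank.

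The analysis named in advance therefore cannot be executed, and whoever analyses the data must choose another test after the fact. That removes the protection that prespecification is meant to give. If someone did force the test by lining up unrelated participants, the result would depend on the order of the data file, and anyone in the larger arm without a partner would be dropped. Satisfaction and usability are named secondary objectives and bear directly on whether the new care models should be rolled out.

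**Working it through.** The plan gives no figure to reproduce here, so the check sets the named test against the stated design and adds a small illustration.

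**Are there pairs?**

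1. *Same person in both groups?* No. Each participant is allocated to one of four arms (Study Design), and no crossover is described.
2. *Matched participants?* No. Randomization describes permuted blocks within strata. If each block of 4 holds one place per arm, a block could be viewed as a loose set, but the article never uses blocks as an analysis unit. For the pooled factorial groups a block would hold two people on each side, so it would not define unique pairs. A missing questionnaire would also break a set.
3. *Change over time within a person?* Technology-acceptance and care-experience questions are repeated at months 6, 12 and 18 (Study Questionnaires). Secondary Outcomes, however, frames both analyses as comparisons between arms. The system usability scale is given once, at month 18, and only to online participants, so it has no second measurement to pair.

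**What does the article do for a similar question?** For drug concentrations, also a rank-based comparison of independent groups, it names the rank-sum test. The two choices in one section do not agree.

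**Illustration (simulated data, not trial figures).** Group sizes are loosely based on the sample size section, where "the total required sample size is 442": 442 / 4 = 110.5 per arm, and 368 / 2 = 184 per pooled factorial group before the 20% inflation. Scores are on a 5-point scale with assumed category probabilities: (0.05, 0.10, 0.20, 0.40, 0.25) for group A and (0.10, 0.13, 0.22, 0.35, 0.20) for group B.

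| Set-up | Signed-rank | Rank-sum |
|---|---|---|
| 110 v 105, both drawn from A's probabilities | cannot be computed; software stops with an array-shape error | not run |
| 184 (A) v 184 (B), same data paired arbitrarily 1000 times | p from 0.16 to 0.49, median 0.29 | p = 0.28, unaffected by order |

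The signed-rank version run here also discards pairs with equal scores. Under the assumed probabilities, the chance that a random pair ties is 0.05×0.10 + 0.10×0.13 + 0.20×0.22 + 0.40×0.35 + 0.25×0.20 = 0.252. About 0.252 × 184 ≈ 46 of the 184 arbitrary pairs would therefore contribute nothing.

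**The case against.** The strongest reply is that this is a slip between two similarly named Wilcoxon tests. The authors name the rank-sum test correctly in the same section, and software would stop on unequal arms rather than return a wrong answer. On that view the p-values that depend on file order are hypothetical, because nothing suggests anyone intends to pair unrelated people. The slip reading is probably right, and it limits the likely practical harm. It does not make the published sentence correct.

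Three limits on scope also stand:

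- For satisfaction, the article says only that arms will be compared. It does not say whether that means the two factorial contrasts, pairwise comparisons or all four arms. Only the arm 3 v arm 4 usability contrast is explicit.
- The article gives no analysis time point for either outcome, so months 6, 12 and 18 are an inference from the questionnaire schedule.
- Stratified or model-based alternatives are a preference. The primary analysis is itself crude, so an unstratified rank-sum test would be consistent with the rest of the plan.

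None of these readings creates pairs. Nor can the point be put down to detail left for an unseen analysis plan, because the article states a specific test.

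**Conclusion.** The concern holds. The named test does not fit the stated comparisons, and nothing elsewhere in the article supplies the pairing it requires. It affects every between-arm analysis of satisfaction and usability. It does not affect the primary noninferiority comparison, its type 1 error or the sample size. It should be corrected, at moderate priority.

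The conclusion rests only on the design and the definition of the test. The simulated p-values depend on assumed score distributions and serve only to show that the result is not unique.

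**What to change.** Replace the sentence naming the test. For each two-group contrast, including usability in arm 3 v arm 4, specify the Wilcoxon rank-sum (Mann-Whitney) test.

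State which contrasts are meant for satisfaction. If they are online v in-clinic and 6-month v 3-month, use a rank-sum test for each. If all four arms are compared at once, use an independent-samples test for several groups such as Kruskal-Wallis. State the time point for each outcome in the same place.

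Two options would make fuller use of the design but are not needed to correct the error: a van Elteren test stratified by PHS and PrEP experience, or a proportional-odds regression containing both factors. Keep the signed-rank test only if within-person change over time is also wanted, and describe that as a separate analysis.

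The cost is a sentence or two in the protocol or analysis plan, with no change to data collection, sample size or the primary analysis.

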### Power and Sample Size Calculation

We assume that the primary outcome measure of unprotected acts will be Poisson distributed with the total number per 100 person-years given as an incident rate (λ) and the total time during monitoring (*t*). We define the incidence rate in the experimental arm as λ_e_ and the incidence rate in the control arm as λ_c_. We aim to reject the null hypothesis that the ratio λ_e_/λ_c_ is greater than or equal to a predetermined noninferiority ratio (r). We consider that a noninferiority ratio of 1.8 is able to preserve clinically acceptable noninferiority bounds with increasing λ.

In a previous PrEP study in the Netherlands (Amsterdam PrEP demonstration project [“AMPrEP study”]), the overall incidence rate of unprotected acts was 78/100 person-years [50]. The AMPrEP study included participants with a high number of sex partners and very high incidence of bacterial STIs. Participants of the NPP have reported fewer casual sex partners and have a lower incidence of bacterial STIs [55]. The EZI-PrEP participants are therefore expected to have fewer unprotected sex acts than the AMPrEP participants. We expect the incidence rate of unprotected acts in the experimental arm (λ_e_) and control arm (λ_c_) to be at least 36/100 person-years. We also assume a median monitoring time of 18 months. Using a Bonferroni-corrected 1-sided type 1 error of 0.0125 (=0.025/2 for a total of 2 comparisons), we will need 368 participants to have 90% power to demonstrate noninferiority using the test statistic based on maximum likelihood estimators from Stucke and Kieser [56]. If λ is higher than 36/100 person-years, we will have sufficient power to demonstrate noninferiority. Considering expected loss to follow-up, we have increased the target sample size by 20%, and thus, the total required sample size is 442.

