### Study Population

We aim to include 442 individuals who are already using PrEP through the Dutch NPP or will be starting or restarting PrEP. Individuals starting PrEP are PrEP naïve (herein referred to as “PrEP starters”), whereas individuals restarting PrEP are persons who have used PrEP more than 6 months prior to inclusion and will recommence PrEP at inclusion (herein referred to as “PrEP restarters”). Both groups of individuals need to have a monitoring consultation after 1 month of starting or restarting PrEP as part of standard-of-care procedures and are therefore grouped in the protocol as “PrEP starters or restarters.” Our intention is that at least 25% of study participants will be PrEP starters or restarters.

The eligibility criteria will be as follows: (1) being eligible for the Dutch NPP (Textbox 1) [45]; (2) being 18 years or older; (3) living in the catchment area of a participating PHS; (4) being able to complete informed consent, medical history, the daily diary, and questionnaires in English or Dutch; (5) having an email address; (6) owning an iOS or Android mobile phone capable of running the study app; (7) having daily access to an internet connection; (8) being able to make online payments; and (9) providing informed consent. The exclusion criteria will be as follows: (1) having an HIV infection; (2) being advised by a physician to wait with starting or restarting PrEP (PrEP starters or restarters) or being advised to stop with PrEP (current PrEP users) for more than 1 month, such as in the case of decreased kidney function with an estimated glomerular filtration rate (eGFR) of less than 60 mL/min/1.73m^2^ or other kidney problems, or chronic use of medication that interacts with TFV/FTC; (3) being advised to have in-clinic monitoring every 3 months, such as in the case of adverse mental health conditions or life circumstances, chronic or acute hepatitis B virus infection, or other medical conditions that require special attention when using PrEP or may need a referral, such as osteoporosis or other bone diseases; and (4) participating in another clinical trial or research project related to HIV prevention.

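### The stated 368 participants for 90% power does not follow from the printed inputs, which give about 306; a 20% increase applied twice would explain the figures but is not proven

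*Protocol article*

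**What the plan says.** All of the calculation stands in the protocol article, Power and Sample Size Calculation.

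- Counts are taken as Poisson. The rate in the experimental and the control group is expected "to be at least 36/100 person-years".
- Exposure: "We also assume a median monitoring time of 18 months".
- Margin: "We consider that a noninferiority ratio of 1.8 is able to preserve clinically acceptable noninferiority bounds".
- Error rate: "Using a Bonferroni-corrected 1-sided type 1 error of 0.0125 (=0.025/2 for a total of 2 comparisons").
- Result: "we will need 368 participants to have 90% power to demonstrate noninferiority", using a cited test statistic built on maximum likelihood estimators.
- Allowance for loss: "we have increased the target sample size by 20%, and thus, the total required sample size is 442".

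The section Study Population repeats the target: "We aim to include 442 individuals". Randomization is to four arms in permuted blocks of 4. The Primary Outcome section compares arms 3 and 4 with arms 1 and 2, and arms 2 and 4 with arms 1 and 3. Each comparison therefore uses the full sample, split 1:1.

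**The concern.** The article prints every input, the type of test and the answer, so the answer can be checked, and it does not come out. The stated requirement lies 20% above what the inputs give, which is too much for rounding. The same 20% is the allowance that the next step adds openly.

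What is at stake is the reported basis of the trial's size. A reader will take 442 to mean 90% power plus a loss allowance. If the inputs are as printed, 442 delivers clearly more than that. If they are not, the section misreports at least one of them. Either way the power statement is wrong as written.

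**Working it through.** **Inputs.** All come from Power and Sample Size Calculation, except the 1:1 split, which follows from the design.

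- Rate λ = 0.36 per person-year in both groups (true ratio 1)
- Exposure t = 1.5 years, so λt = 0.54 expected acts per participant
- Margin R = 1.8
- One-sided alpha 0.0125, z = 2.2414
- Power 90%, z = 1.2816
- (2.2414 + 1.2816)² = 12.411

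**Attempt to reproduce 368** (n is per group):

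1. Unrestricted maximum likelihood (Wald): n = (zα + zβ)² (1 + R²) / [λt (R − 1)²] = 12.411 × 4.24 / (0.54 × 0.64) = 152.3. Rounded up, this is 153 per group, **306** in total.
2. Restricted maximum likelihood: n = (zα√(2R) + zβ√(1 + R²))² / [λt (R − 1)²] = (2.2414 × √3.6 + 1.2816 × √4.24)² / (0.54 × 0.64) = 137.4. Rounded up, 138 per group, **276** in total.
3. Log rate ratio: n = 2(zα + zβ)² / [λt (ln R)²] = 2 × 12.411 / (0.54 × 0.5878²) = 133.05. Rounded up, 134 per group, **268** in total.
4. Further forms: log ratio with restricted variance 282; square-root transform 276.
5. Misreading 0.0125 as two-sided (0.00625 one-sided) in the Wald form: 352.

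None of these gives 368.

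**Power at the stated sizes.** For the Wald form, power = Φ[(R − 1)√(λt·n / (1 + R²)) − zα].

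| Total N | Wald formula |
|---|---|
| 306 | Φ(3.531 − 2.241) = 90.1% |
| 354 | Φ(3.798 − 2.241) = 94.0% |
| 368 | Φ(3.873 − 2.241) = 94.9% |
| 442 | Φ(4.244 − 2.241) = 97.7% |

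At 368 the restricted form gives 96.5% and the log form 97.1%. Enumerating the Poisson distribution exactly at 368 gives 96.1% for the Wald test and 96.8% for the restricted test. All lie well above 90%.

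**Where 368 might come from.**

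- 306 × 1.2 = 367.2, rounded up to 368. Per group, 153 × 1.2 = 183.6, rounded up to 184, and 2 × 184 = 368.
- 368 × 1.2 = 441.6, rounded up to 442.

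Both steps match to the unit.

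**Other inputs that come close.** None of these is stated. In the Wald form, a rate of 30 per 100 person-years gives 366, an exposure of 15 months gives 366, and a mean exposure of about 1.245 years gives 368.

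**The case against.** The mismatch itself is hard to dispute, but four points limit what can be drawn from it.

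**The double increase is an inference.** Nowhere does the section say that 368 already contains an allowance for loss. It gives 18 months as a median, while the diary that measures the outcome runs for 18 months only. If 18 months is also the maximum, mean exposure falls below 1.5 years whenever someone leaves early, and a mean near 1.245 years would give 368. This stands. It does not rescue the section, because such an input would then be missing from it.

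**The cited method paper is not at hand.** Equating the named test with the unrestricted Wald form is therefore an assumption. This stands for the exact value 306, but not for the mismatch, because the other forms checked at the stated alpha need fewer participants.

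**A reader might infer that 442 is too small after losses**, since 442 × 0.8 = 354, which is below 368. The documents do not support this. They speak of an increase of 20%, not of a 20% loss rate, and an increase of 20% offsets a loss of 16.7% (1 − 1/1.2). The Primary Outcome section also counts the time and data of those who leave up to their last day. If 20% left halfway on average (an assumption), the exposure would equal 442 × 0.9 = 398 full participants.

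**A reader might also infer that the hidden surplus is the trial's only protection against unfavourable conditions.** That goes too far. The planning rate of at least 36 is itself set low against the 78 per 100 person-years in the earlier Dutch study. At 78 the Wald form needs only 142 participants.

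Finally, the error is conservative and alters no estimate, test or decision rule. That is correct, and it limits the weight of the point to a correction of the reported calculation.

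**Conclusion.** The point holds in limited form. The figure of 368 for 90% power is not reproduced by the printed inputs. The Wald form on unrestricted maximum likelihood estimators gives 306, and the other standard forms give 268 to 282. The stated requirement is thus 20% above the largest of these, and power at 368 is about 95% to 97%.

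This rests on the section's own assumptions: Poisson counts, equal true rates of 0.36 per person-year, 1.5 years each and 1:1 comparisons on the full sample. A 20% increase applied twice is the simplest explanation and fits both steps exactly, but it remains unproven.

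The trial is not underpowered under these assumptions. The defect is a sample size statement that is wrong as written.

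**What to change.** In Power and Sample Size Calculation, do one of two things:

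1. State the inputs that actually give 368 (for example the mean exposure or the rate used), with the form of the test; or
2. Correct the evaluable requirement to about 306, apply the loss allowance once, keep 442 as the target, and restate the power it delivers. By the Wald form under Poisson counts this is about 97.7% with full follow-up, and about 94% if the equivalent of 354 fully followed participants remain.

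The cost is one corrected paragraph. Enrolment stays as planned.
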